### Outcomes

#### Primary outcome

(1) The primary outcome is the mean duration (days) of achieve the caloric goal in every group. The caloric goal of 25 kcal/kg (ideal body weight) for caloric need was calculated by a single nutritionist. The duration will be the first 5 days after the intervention.

#### Secondary outcome

Secondary outcomes include the following: (1) the rate of onset of gastric residual (%) (defined as volume >500 mL) among the three groups; (2) abdominal pressure, (mmHg) as measured through the indirect bladder pressure, whereby the bladder urine will be emptied in the supine position, and 50 mL saline will be poured into the balloon catheter to the pubic symphysis as the base point, keeping the piezometric tube perpendicular to the ground to obtain indirect abdominal pressure; (3) the rate of onset of pneumonia in each group (%), as defined by two of the following clinical criteria, fever (> 38.3 °C) or hypothermia (≤ 36.0 °C) and leucocytosis (> 10×10^9^ cells/L) or leucopenia (≤ 4×10^9^ cells/L) and purulent tracheal aspirate or sputum. These factors are associated with the appearance of a new infiltrate or changes in the existing infiltrate on chest X-ray [11]; (4) the proportion (%) of individuals who achieve the caloric goal. The caloric goals using 25 kcal/kg (ideal body weight) for caloric need were calculated by a single nutritionist; (5) motilin levels before and 5 days after intervention; (6) the length of the ICU stay (in days) up to 12 weeks; and (7) the ICU mortality rate (%) at 28 days after intervention and survival analysis up to 12 weeks (Fig. 1). Follow-up by visit or telephone will be conducted at 28 days and 12 weeks after the intervention.

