## Objectives

The primary objective of the DFM-GFC study is to determine whether cyclic or intermittent feeding can extend the duration (days) of achieve caloric goal compared with continuous feeding. The secondary objective of the study is to assess whether the two feeding methods can increase the proportion of patients who achieve the caloric goal, shorten the length of stay in the ICU, and reduce the incidence of feeding complications, including the rates of onset of gastric residua and pneumonia. Abdominal pressure, motilin levels, and mortality in three groups will also be explored.

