### Inclusion criteria

The following inclusion criteria will be applied: participants (1) aged 18–80 years, (2) with Acute Physiology and Chronic Health Evaluation (APACHE)-II ≥ 15 [10], (3) in whom EN can be used after evaluation, (4) with an expected ICU stay of > 48 h, and (5) patients or family members signed informed consent.

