### Exclusion criteria

The following exclusion criteria will be applied: participants (1) required to fast clinically, such as those with digestive tract perforation, bleeding, or gastrointestinal tract surgery; (2) who are allergic to EN preparations; (3) have unstable hemodynamics; (4) who are unwilling to participate in the trial or cannot cooperate with the treatment, and (5) who are pregnant and lactating.

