### Interventions

Patients will be randomized into three arms: a continuous feeding group, cyclic feeding group, and intermittent feeding group. In the continuous group, an electric infusion feeding pump will deliver EN at a constant hourly rate of 24 h/day. The critical patients who are randomized to the cyclic feeding group will receive the EN preparation for 16 h via continuous pumping through the stomach tube every day. The initial pumping speed of the two groups will be calculated as the average pumping volume of the total enteral nutrition in 1 day. For example, if the total daily intake is 1200 mL, the initial pumping speed of the continuous group will be 50 mL/h, which of cyclic is 75 mL/h. The gastric residual volumes (GRV) will be checked every 4 h. If it is not tolerable, the pumping speed will be reduced by half of the original speed. Feeding intolerance will be defined as GRV > 250 mL; EN will be stopped and reassessed after 4 hours if GRV > 500 mL. The critical patients who are randomized to the intermittent feeding group will be administered the EN preparation through four meals every day (at 08:00, 12:00, 18:00, and 22:00). In the intermittent group, the daily amount of feeding will be divided into four meals, and each meal will be pumped through the stomach tube within 60 min or 120 min. The following EN preparation pumping scheme will be used. If the volume of each meal is less than or equal to 250 mL (≤ 250 mL), it will be delivered within 60 min; if the volume is greater than 250 mL (> 250 mL), it will be delivered within 120 min. If the total daily intake is 1200 mL, the initial pumping speed will be 150 mL/h. GRV will be checked before each intermittent feeding. If it is not tolerable, the pumping speed will be reduced by half of the original speed. If GRV > 500 mL, EN will be stopped and reassessed after 4 hours. All feeding will be started within 24 h of ICU admission. An EN suspension ((SP, Peptisorb), Nutricia Pharmaceuticals (Wuxi, Jiangsu, China) Co. Ltd) will be used, with a calorie content of 1 kcal/mL and a thermal nitrogen ratio of 133:1. Each bottle will contain 500 mL of nutrition preparation consisting of 61.5 g carbohydrate, 20.0 g protein, and 19.45 g fat (Wuxi). The nutritional preparations for the three groups of patients will be pumped into the nasal feeding tube through a volumetric pump (brand: Braun, origin: Melsungen AG, Germany). The treatment course will be 5 days (Table 1).

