## Discussion

Although guidelines state that EN should be given by a pump or gravity drip, there is no agreement on whether continuous pumping should be applied or on the duration of pumping. The DFM-GFC study will explore the impact of three common EN delivery methods (continuous, intermittent, cyclic) on heat entrapment, gastrointestinal complications, and the occurrence of aspiration and aspiration pneumonia. In addition, costs associated with EN delivery (equipment use and complications) will be compared. Although the incidence of complications will not decline significantly, the cost of treatment will be lower if the intermittent pumping and cyclic pumping feeding method are accomplished in less time than the continuous pumping feeding method.

Current guidelines often compare continuous feeding to intermittent feeding (done either via manually set gravity rate or volumetric pump) [1]. The number of volumetric pumps available may vary from institution to institution. However, the use of a volumetric pump in place of manual infusion (gravity drip) for intermittent feedings allows for more consistent feeding. All three feeding methods, continuous, intermittent, and cyclic are commonly used in hospitals [14, 15]. Nonetheless, with the application of a volumetric pump, manual injection is no longer used for intermittent feeding, and the time of each injection can also be extended to several hours. Continuous feeding, intermittent feeding, and cyclic feeding have become three common feeding methods. Some studies [13, 16, 17] have demonstrated that continuous pumping does not improve blood sugar levels, stomach retention, or the occurrence of ventilator-associated pneumonia.

According to an individual’s physiology and habits, it is necessary to rest during the inter-meal time, the physiologically appropriate number of meals per day for humans is an enigma. According to Homer, only two, rather than three, meals were eaten per day in ancient Greece. During sleep, peristalsis of the gastrointestinal tract is slowed, and secretion of digestive juices is reduced. Some studies [18] have demonstrated that there is no difference in the amount of water in the small intestine and the amount of hormones secreted by the small intestine using continuous pumping and bolus through a gastric tube in healthy individuals. Therefore, is intermittent eating the result of physical conditions and social behavior or the physiological needs of organs?

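### The pneumonia outcome is labelled as onset, but its definition lets a pneumonia present at ICU admission count as an event

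*Protocol article*

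**What the plan says.** All references are to the protocol article.

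- **Objectives.** The secondary objective asks whether cyclic and intermittent feeding "reduce the incidence of feeding complications, including the rates of onset of gastric residua and pneumonia". The Discussion names the mechanism of interest as "the occurrence of aspiration and aspiration pneumonia".
- **Secondary outcome (3).** The outcome is "the rate of onset of pneumonia in each group (%), as defined by two of the following clinical criteria": abnormal temperature, abnormal white cell count, purulent secretions. The radiographic part follows: "These factors are associated with the appearance of a new infiltrate or changes in the existing infiltrate on chest X-ray".
- **Inclusion and exclusion criteria.** Inclusion rests on age, APACHE-II of at least 15, suitability for enteral nutrition, consent, and patients "with an expected ICU stay of > 48 h". The five exclusions cover need to fast, allergy to the preparation, unstable haemodynamics, unwillingness or inability to cooperate, and pregnancy or lactation. Neither list mentions pneumonia, infection or an infiltrate at admission.
- **Interventions.** "All feeding will be started within 24 h of ICU admission".
- **Statistical analysis.** Count outcomes are compared between groups by chi-square.

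**The concern.** The label and the case definition point in different directions. Onset, and incidence in the Objectives, describe new events after feeding begins. The definition also accepts a change in an infiltrate that is already there. Because feeding starts within a day of ICU admission, an admission pneumonia would usually still be active. A patient with fever, leucocytosis and an evolving admission infiltrate therefore meets the stated criteria, although the disease came before the first feed.

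At stake is how the pneumonia result can be read. If a share of each arm's events is admission disease, the arms look more alike than they are for new pneumonia. A finding of no difference could then be taken as reassurance about aspiration risk in a trial that the Discussion says will serve as a basis for feeding guidelines.

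**Working it through.** **Is there a figure to reproduce?** No. The article states no pneumonia rate, effect or power; its power statement concerns the time to the caloric goal. What follows is an illustration. Only the 30 patients per arm come from the document (Sample size).

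**Can an admission case meet the definition?**
1. Entry: nothing in either eligibility list stops a patient with pneumonia from being randomised.
2. Clinical signs: two of three are required, and all three are ordinary features of an active pneumonia.
3. Radiograph: a change in an existing infiltrate is enough.
4. So the case counts, unless the word onset is applied as a further condition. The definition does not say how it would be.

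**Inputs (assumed):** rate of new pneumonia r = 20% vs 10% in patients free of it at entry; share with pneumonia at entry p = 20%, 30% or 50%; share of those entry cases that get counted c, the same in both arms.

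**Formulas:**
- Observed rate = p·c + (1 − p)·r
- SE of the difference = √{[a(1 − a) + b(1 − b)]/n}, where a and b are the two rates and n is the number per arm

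**Upper bound, c = 1, n = 30 per arm.** For p = 20%: 0.20 + 0.80 × 0.20 = 0.36 and 0.20 + 0.80 × 0.10 = 0.28. SE = √[(0.2304 + 0.2016)/30] = 0.120, so difference/SE = 0.08/0.120 = 0.67.

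| p | Observed rates | Difference | Risk ratio | Difference/SE, as written | Free of pneumonia at entry, per arm | Difference/SE, restricted |
|---|---|---|---|---|---|---|
| 20% | 36% vs 28% | 8 points | 0.78 | 0.67 | 24 | 0.98 |
| 30% | 44% vs 37% | 7 points | 0.84 | 0.55 | 21 | 0.92 |
| 50% | 60% vs 55% | 5 points | 0.92 | 0.39 | 15 | 0.77 |

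The true values are a 10-point difference and a risk ratio of 0.50. The restricted column keeps 20% vs 10% with n = 30(1 − p); for p = 20%, SE = √[(0.16 + 0.09)/24] = 0.102 and 0.10/0.102 = 0.98.

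**If only half of the entry cases are counted (c = 0.5).** Rates are 26% vs 18%, 29% vs 22% and 35% vs 30%; risk ratios are 0.69, 0.76 and 0.86; difference/SE is 0.75, 0.62 and 0.41. The absolute difference is again 8, 7 and 5 points, because it equals (1 − p) × 10 points whatever c is. Counting the entry cases affects the risk ratio and the noise.

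**Power, from Φ(d − 1.96) + Φ(−d − 1.96) with d = difference/SE.** As written with c = 1: about 10%, 9% and 7%. Restricted: about 17%, 15% and 12%. If nobody had pneumonia at entry, 30 per arm would give d = 0.10/√(0.25/30) = 1.10 and about 19%.

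**The case against.** **The wording points to new events.** Onset and incidence both suggest that a pneumonia diagnosed before randomisation is not meant to count. An existing infiltrate need not be pneumonia either, and the clause may be there so that a new event can be detected on a film that is already abnormal. This is a fair reading of intent, but the criterion does not carry it out: it has no baseline status with which to tell the two situations apart.

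**The full protocol or analysis plan may supply the detail.** The article is condensed, the SPIRIT schedule is not visible here, and the definition cites a source not at hand. The absence of a stated counting window is therefore not in itself the point. The point rests on what the article does state, namely the case definition and the eligibility lists, which together admit the mixing.

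**Randomisation takes care of it.** A reader might infer that admission pneumonia biases the comparison. The documents do not support that: it is balanced in expectation, and the chi-square error rate already allows for chance imbalance. The SD of the between-arm difference in entry prevalence, √[2p(1 − p)/30], is 10 to 13 points for the p values used. That is noise. It cannot be measured against an effect sought on pneumonia, because the article states none.

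**Such cases may still be feeding events.** A reader might also infer that a changing admission infiltrate can have nothing to do with the feeding method. That goes too far. A patient admitted with pneumonia can still aspirate feed, and the change may be that event. This is a reason to report these changes separately, not to discard them.

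**The gain is small in absolute terms.** This stands. Under the assumed 20% vs 10%, power is low with or without the fix. The fix gives a cleaner estimate of new pneumonia, not an adequately powered test.

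**Conclusion.** The point holds as a definitional fault in one secondary outcome. An outcome presented as new pneumonia and as a feeding complication uses a criterion that an evolving admission pneumonia can meet, in a population from which such patients are not excluded. The consequence is dilution and added noise, not systematic bias between arms.

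On assumed rates of 20% vs 10%, with 20% to 50% of patients entering with pneumonia, the 10-point difference shrinks to between 8 and 5 points. If every entry case is counted, which is an upper bound, the risk ratio moves from 0.50 to between 0.78 and 0.92. These sizes rest wholly on assumed rates and on entry cases being counted equally often in each arm; if feeding method also affects worsening in those patients, the dilution would differ. The primary outcome is not touched. The definition should be corrected, but the trial's main conclusion does not depend on it.

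**What to change.** In Secondary outcome (3):
1. Record pneumonia status (yes/no) before the first feed.
2. Define the outcome as new pneumonia first meeting the criteria after the first feed, within one fixed window that is the same in all arms.
3. For the main analysis of this outcome, use patients without pneumonia at randomisation as the denominator. The restriction depends only on pre-treatment status, so the randomised comparison is kept.
4. Report worsening of an existing pneumonia or infiltrate separately by arm, since some of it may be feed aspiration.
5. If a minimum lag after the first feed is wanted, pre-state it as a sensitivity analysis. As the main definition it would drop early aspiration events, which matters when the treatment course lasts 5 days.

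**Cost:** one baseline item and a change of outcome wording. The denominator falls (to 24, 21 or 15 per arm in the scenarios above) and there are fewer events. On those assumptions the difference/SE still rises, from 0.67, 0.55 and 0.39 to 0.98, 0.92 and 0.77. Feeding and patient care do not change, nor does the primary analysis.

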#### Sample size

The sample size was calculated based on the duration required to achieve the caloric goal. Because there are few studies about cyclic feeding, we referred to the studies on intermittent and continuous groups. It was assumed that the time to achieve the caloric goal would be consistent with earlier RCTs [12]: 4 days (intermittent feeding group) and 3 days (continuous feeding group). Twenty-six evaluable patients per group will provide 90% power for detection at a 5% two-sided significance level. Therefore, the total sample size will be 84. Based on the sample sizes in previous studies and an estimated dropout rate extrapolated from feasibility data of 8–10% [13], we expect that 30 patients will be enrolled in each arm and that the total sample size will be at least 90.

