### Statistical analysis

All statistical analyses will be performed using SPSS 20.0 software. Measurement data will be expressed as the mean ± standard deviation. Normality tests and homogeneity tests of variance will also be performed. In cases of normal distribution and homogeneity of variance, a *t* test will be conducted; otherwise, a non-parametric test will be employed. If the measurement data conform to a normal distribution, an independent sample *t* test will be applied between two groups; one-way analysis of variance (ANOVA) will be utilized between the three groups. In the case of non-normal distribution, two groups will be compared using the Mann–Whitney *U* test, and the three groups will be compared with the Kruskal–Wallis test. Enumeration data between two and three groups will be compared using chi-square/Crosstab statistical analysis, and the results will be expressed as the frequency constituent ratio (%). *P* < 0.05 will indicate statistical significance.

For patients who die or are lost to follow-up, their observation time will be censored at the time of death or date of last contact. For patients with early withdrawal who are lost to follow-up, intention-to-treat analysis (ITT) will be applied. For the second endpoint (6), cumulative proportion survival curves according to Kaplan–Meier analysis will be obtained for each group and compared with the log-rank test. To explore the group effect on the time to the event of composite outcome, with adjustment for baseline covariates, the Cox regression model will be used.

The trial will be prematurely paused or closed by the DSMB to evaluate safety information from the study or if there is evidence of harm in the study. The principal investigator (PI) will be able to access these interim results.

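### Motilin is measured before and after the intervention, but the group tests named for it are unadjusted; ANCOVA on the baseline value would generally be more precise at almost no cost

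*Protocol article*

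**What the plan says.** The protocol article, Secondary outcome, lists as item (5) "motilin levels before and 5 days after intervention". The Objectives section places motilin among the measures to be explored across the three groups.

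The Statistical analysis section has one set of rules for all measurement data and does not mention motilin by name. Under normality, "an independent sample *t* test will be applied between two groups" and "one-way analysis of variance (ANOVA) will be utilized between the three groups". Otherwise two groups are compared by Mann–Whitney, and "the three groups will be compared with the Kruskal–Wallis test".

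Baseline covariates appear only once in that section, for a time-to-event composite: "with adjustment for baseline covariates, the Cox regression model will be used". No ANCOVA, change score, paired or repeated-measures analysis is named for any measurement outcome.

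**The concern.** The trial collects a baseline motilin value, but none of the tests named for measurement data has a term for it. If baseline and day-5 motilin are correlated, part of the spread in the day-5 values is predictable from the baseline. Removing that part narrows the confidence interval without any further sample or patient.

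The arms are small and were sized for another outcome, so the precision for motilin is whatever that sample happens to give. In small arms, chance differences in baseline motilin are also likely. An unadjusted estimate carries part of such a difference, while an adjusted one largely removes it.

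**Working it through.** **The plan's own figure.** No sample size, standard deviation (SD) or power is given for motilin. The only such statement concerns the primary outcome: "Twenty-six evaluable patients per group will provide 90% power for detection at a 5% two-sided significance level". The assumed difference there is 4 − 3 = 1 day, with no SD. Solving backwards by the normal approximation, SD = √(26/2) / (1.960 + 1.282) = 3.606 / 3.242 ≈ 1.11 days (1.09 with the t distribution). The figure can therefore be neither confirmed nor refuted. I use 26 only as the planned number of evaluable patients per arm. It fits the enrolment of 30 per arm less 8–10% dropout, which is 27.6 to 27.0.

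**Inputs.**
- Two motilin values per patient, before and 5 days after (Secondary outcome).
- Unadjusted tests (Statistical analysis).
- 26 evaluable per arm (Sample size), carried over from the primary outcome.
- Correlation r between the two values: not in the document; assumed 0, 0.3, 0.5 and 0.7.
- Equal variance at both times: assumed.

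**Formulas.** Set the variance of a between-arm difference in day-5 means to 1. Then:
- change score: 2(1 − r)
- ANCOVA: 1 − r²
- ANCOVA relative to change score: (1 − r²) / [2(1 − r)] = (1 + r)/2
- unadjusted patients per arm that 26 adjusted patients are worth, against a day-5-only comparison: 26/(1 − r²)

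**Results.**

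| r | Day-5 only | Change score | ANCOVA | Cut vs day-5 only | Cut vs change score | 26 per arm work like |
|---|---|---|---|---|---|---|
| 0 | 1.00 | 2.00 | 1.00 | 0% | 50% | 26 |
| 0.3 | 1.00 | 1.40 | 0.91 | 9% | 35% | 29 |
| 0.5 | 1.00 | 1.00 | 0.75 | 25% | 25% | 35 |
| 0.7 | 1.00 | 0.60 | 0.51 | 49% | 15% | 51 |

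A change-score comparison uses the baseline, but for r below 0.5 it is less precise than ignoring the baseline altogether.

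**Simulation check.** With three arms of 26 and 20,000 runs at r = 0.3, 0.5 and 0.7, the ANCOVA variance relative to day-5 only was 0.92, 0.76 and 0.51. For change scores it was 1.41, 1.00 and 0.59. Both agree with the formulas; the small excess for ANCOVA is the price of estimating the slope.

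**Detectable difference.** For one pairwise comparison at 80% power and two-sided 5%, the day-5-only comparison detects (1.960 + 0.842) × √(2/26) ≈ 0.78 SD. Multiplying by √(1 − r²) gives 0.74, 0.67 and 0.56 SD at r = 0.3, 0.5 and 0.7.

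**Chance imbalance.** With 26 per arm, the baseline difference between two arms has standard error √(2/26) ≈ 0.28 SD. A day-5-only estimate carries r times the gap. A gap of one standard error therefore moves it by about 0.08, 0.14 and 0.19 SD at r = 0.3, 0.5 and 0.7.

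**The case against.** **This belongs in the analysis plan.** The article condenses a fuller protocol, and the covariates for each secondary endpoint are often left to the statistical analysis plan, which is not at hand. That would settle the matter if the article were silent. It is not: it names the tests for measurement data and all are unadjusted, while covariate adjustment is reserved for the Cox model. A later plan may well improve on this, but it would be departing from the stated method.

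**The baseline may not be discarded.** A reader might infer that the plan throws the baseline value away. The text does not support that. The rules are generic, and an outcome defined by a before and an after value fits an ANOVA on the change, which does use the baseline. What stands is narrower: whichever value is tested, ANCOVA is generally the more precise choice.

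**The unadjusted tests are valid.** A reader might also infer bias or a distorted error rate, or that baseline imbalance passes in full into the result. None of this follows. Randomisation makes the unadjusted comparison unbiased, its type I error already allows for chance imbalance, and a day-5-only estimate carries the gap only in proportion to r.

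**The gain may be small.** This stands. No correlation is given, and a value below about 0.3 is possible over 5 days in critically ill patients. The gain over a day-5-only comparison is then 9% or less, and nil at r = 0.

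**Conclusion.** The point holds as a free improvement on a secondary outcome. The named comparison is valid but generally less precise than the collected data allow.

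The size of the loss depends on which value is tested and on r, and the article gives neither. Over the assumed range it runs from nothing to about half of the variance against a day-5-only comparison, and from 50% down to 15% against a change score. These percentages rest on equal variances at the two times and a common linear relation between them. They do not depend on the number of patients, but the equivalent sample sizes do. Those use 26 evaluable per arm, and the number with both motilin samples could differ. The formulas describe comparisons of means and do not carry over exactly to the Mann–Whitney or Kruskal–Wallis tests.

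**What to change.** In the Statistical analysis section, state that day-5 motilin is compared between arms by ANCOVA, with arm as factor and baseline motilin as covariate, both motilin values being log-transformed if skewed. Report adjusted differences (ratios on the log scale) for cyclic and for intermittent versus continuous feeding, with 95% confidence intervals. This also settles which motilin value is tested.

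The cost is one sentence and one degree of freedom. No new samples or patients are needed. The sentence should be fixed before any comparison of motilin by arm, through the route in the Protocol amendments section. If a separate analysis plan already specifies this model, the two texts only need to be brought into line.

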**Methods:**

Different Feeding Methods on Gastrointestinal Function of Critical patients (DFM-GFC) is a randomized clinical study that will be performed to assess the effects of three feeding methods on critically ill patients. A total of 90 critically ill patients will be equally randomized into three groups: continuous feeding, cyclic feeding, and intermittent feeding. The patients will be administered a gastrointestinal nutrition preparation over 24 h via a gastric tube or over 16 h via an intermittent pump. The primary outcome is the mean duration (days) to reach the caloric goal in each group. Secondary outcomes include the rate of onset of gastric residual, abdominal pressure, the rate of onset pneumonia, and the proportion of individuals achieving the caloric goal. Additionally, the length of intensive care unit (ICU) stay and mortality rate at 28 days post-enrolment will be evaluated.

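### The 28-day mortality outcome is defined differently in the abstract and in secondary outcome (7), and the ICU-only version leaves out deaths after ICU discharge

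*Protocol article*

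**What the plan says.** The Secondary outcome section gives item (7) as "the ICU mortality rate (%) at 28 days after intervention and survival analysis up to 12 weeks". The abstract, under Methods, says that "the length of intensive care unit (ICU) stay and mortality rate at 28 days post-enrolment will be evaluated". The Objectives give neither place of death nor time point: "Abdominal pressure, motilin levels, and mortality in three groups will also be explored".

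Three other statements bear on the clock. Under Interventions, "The treatment course will be 5 days" and "All feeding will be started within 24 h of ICU admission". Under Primary outcome, the window for reaching the caloric goal is described as "The duration will be the first 5 days after the intervention".

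On ascertainment, the Secondary outcome section says "Follow-up by visit or telephone will be conducted at 28 days and 12 weeks after the intervention".

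The Statistical analysis section attaches the Kaplan–Meier curves and log-rank test to outcome (6), which is length of ICU stay, and says that the observation time of patients who die is censored at death. It does not name death as the event for outcome (7).

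**The concern.** A mortality outcome needs one rule for which deaths count and one starting point. Here the abstract and the outcome list give different answers to both.

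The ICU restriction is the part that can affect the comparison between arms. A 28-day rate limited to ICU deaths depends on how long patients remain in the ICU. The Objectives ask whether cyclic or intermittent feeding shortens ICU stay, so exposure to the counted event may itself differ by arm. Earlier discharge would then lower the ICU death rate even if no life were saved.

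There is also a reporting risk. With two published definitions, the choice could be made after the data are known. The feeding arms are not blinded to the treating team, and the Statistical analysis section lets the principal investigator see interim results.

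**Working it through.** The protocol states no mortality figure, so there is nothing to reproduce. The check sets the statements side by side and then sizes each difference.

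**Step 1. The statements.**

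| Place | Deaths counted | Clock starts | Horizon |
|---|---|---|---|
| Abstract, Methods | Any, on the natural reading | Enrolment | 28 days |
| Objectives | Not stated | Not stated | Not stated |
| Outcome (7), first part | ICU deaths | Intervention (start or end not stated) | 28 days |
| Outcome (7), second part | Survival, place not stated | Not stated | 12 weeks |
| Statistical analysis | Time-to-event methods tied to outcome (6); deaths censored | Not stated | Not stated |

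**Step 2. Place of death.** Take a patient who leaves the ICU on day 10 and dies on the ward on day 20. The abstract's rate counts this death. The ICU rate in outcome (7) does not.

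Inputs: 30 patients per arm (Sample size section); 3% to 10% of patients dying between ICU discharge and day 28 (assumption, not in the document).

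- 30 × 0.03 = 0.9 deaths per arm
- 30 × 0.10 = 3 deaths per arm
- Each death moves an arm's rate by 1/30 = 3.3 percentage points

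To show the effect on a comparison, suppose two arms each have 9 deaths in 30 by day 28 (30%, assumed). In one arm 1 death follows ICU discharge; in the other, which discharges earlier, 3 do.

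- All-cause: 9/30 = 30.0% in both arms
- ICU only: (9 − 1)/30 = 26.7% against (9 − 3)/30 = 20.0%

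The apparent difference of 6.7 points comes entirely from where the patients died.

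**Step 3. Time origin.** There are two readings.

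- *Clock from the start of feeding.* The primary outcome wording "The duration will be the first 5 days after the intervention" covers the treatment days themselves, so there the clock appears to start with feeding. The gap to enrolment is then taken as about 1 day. This is an assumption: feeding is tied to ICU admission (within 24 h), and no interval from enrolment to feeding is given.
- *Clock from the end of the course.* Day 28 would then fall at 28 + 5 = day 33 from the start of feeding.

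To size both, assume a constant hazard and 28-day mortality m of 10% to 40% (not in the documents). Mortality at day 28 + k is 1 − (1 − m)^((28 + k)/28).

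| m | k = 1 day | k = 5 days |
|---|---|---|
| 10% | 10.34% (+0.3 points) | 11.68% (+1.7 points) |
| 40% | 41.08% (+1.1 points) | 45.23% (+5.2 points) |

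Across all 90 patients this is about 0.3 to 1.0 extra deaths for 1 day and 1.5 to 4.7 for 5 days.

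**Step 4. Direction.** The two differences work in opposite directions. A later clock adds late ICU deaths that the abstract's rate would miss; the ICU restriction drops post-discharge deaths that the abstract's rate would count.

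**The case against.** The best defence is that the outcomes section is the operative definition and the abstract a shortened version of it. Abstracts often drop qualifiers, and in "the length of intensive care unit (ICU) stay and mortality rate at 28 days post-enrolment will be evaluated" the word ICU might be meant to govern mortality as well as stay. That is possible but strained. It would remove the place-of-death conflict between the two sections, but not the different time origin, nor the dependence of an ICU-only rate on ICU stay.

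A reader might infer that the horizons are day 28 and day 33, a shift of 5/28 = 18%, and that deaths during the feeding course are excluded. The document does not support that as its plain meaning. The primary outcome uses the same phrase for the treatment days, and the motilin measurement 5 days after intervention also fits a clock that starts with feeding, given a 5-day course. The 5-day gap is an upper bound under the less likely reading.

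A reader might also infer that outcome (7) contradicts itself by joining ICU mortality to 12-week survival. It does not: these are two components, and reporting both is common. Post-discharge deaths can still enter the 12-week analysis; they are missing only from the 28-day rate.

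ICU mortality is a recognised endpoint in critical care, so its use alone is not an error. Mortality here is one of seven secondary outcomes and does not drive the sample size. Fig. 1, which outcome (7) cites, is not shown and may fix the time points. These points limit the weight of the concern, but no visible text resolves the difference.

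**Conclusion.** The concern holds in limited form. The abstract and outcome (7) differ in time origin and, on the natural reading of the abstract, in which deaths count.

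The place-of-death difference is the firmer and more consequential one, because ICU-only mortality depends on an outcome the trial hopes to change. Its size is not known from the document: about 1 to 3 deaths per arm of 30 if 3% to 10% of patients die between ICU discharge and day 28. The time-origin difference is probably about a day and at most about 5 days, depending on a phrase the protocol does not define.

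The primary outcome and the sample size are unaffected. The point should be corrected before the mortality analysis, but it does not threaten the trial's main comparison.

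**What to change.** Define the 28-day component of outcome (7) as death from any cause, in or out of the ICU, within 28 days of randomisation. Run the 12-week survival analysis from the same origin, with death as the event, and attach it explicitly to outcome (7) in the Statistical analysis section. Use the same definition in the abstract and the outcomes section. Keep ICU mortality, if wanted, as an additional descriptive measure.

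The cost is essentially wording, plus the ethics committee approval that the Protocol amendments section requires. The 28-day and 12-week contacts are already planned, and the 12-week survival analysis already needs vital status. The date of death should be recorded, so that time can be counted from randomisation whenever the contact takes place. Settle the definition before mortality is compared by arm.
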